### Home-Based Intervention

#### Overview

The interventions will be delivered through Canvas, which is a secured, commercialized learning management system. First, all participants will receive weekly notifications when a new module is available on Canvas, including exercise videos and educational studies. The weekly notifications can be delivered through the Canvas system and email. Third, participants will be able to leave comments and questions on exercise videos, educational studies, and post workout comment section. Fourth, to ensure any questions or technical issues can be addressed in a timely manner, participants will be able to reach the study team via multiple communication channels, including a study phone number, email, or messaging via the Canvas system.

#### Prerecorded, Asynchronous M2M Videos

Both groups of participants receive the same exercise prescriptions at the first phase of the intervention. The M2M program provides a sequence of exercise routine, which is accompanied by music to improve range of motion, muscular strength and endurance, cardiovascular capacity, and balance or proprioception. The weekly exercise video is set to progressively increase the exercise minutes to enable the participants to reach and exceed the recently published SCI exercise guideline [38]. Both groups of participants will begin with 30 minutes of exercise (twice weekly or 15 minutes per session) and increase the minutes incrementally until they reach the SCI guideline of 90 minutes at week 6 (3 times weekly or 30 minutes per session) and 150 minutes at week 9 (3 times weekly or 50 minutes per session). The detailed exercise prescription is presented in Table 1.

**Table 1 table1:** Description of exercise components and prescriptions in minutes per week.

Exercise Component	Week 1, minutes	Week 2, minutes	Week 3, minutes	Week 4, minutes	Week 5, minutes	Week 6, minutes	Week 7, minutes	Week 8, minutes	Week 9, minutes	Week 10, minutes	Week 11, minutes	Week 12, minutes
ROM I^a^	5	5	5	5	5	N/A^b^	N/A	N/A	N/A	N/A	N/A	N/A
ROM II	N/A	N/A	N/A	5	5	5	5	5	5	5	5	5
Muscular Strength I	5	5	5	5	N/A	N/A	N/A	N/A	N/A	N/A	N/A	N/A
Muscular Strength II	N/A	N/A	N/A	N/A	5	5	5	5	N/A	N/A	N/A	N/A
Muscular Strength III	N/A	N/A	N/A	N/A	N/A	N/A	N/A	N/A	5	5	5	5
Aerobic I	N/A	N/A	N/A	5	5	N/A	N/A	N/A	N/A	N/A	N/A	N/A
Aerobic II	N/A	N/A	N/A	N/A	N/A	10	10	10	10	10	10	10
Aerobic III	N/A	N/A	N/A	N/A	N/A	N/A	N/A	N/A	10	10	10	10
Aerobic IV	N/A	N/A	N/A	N/A	N/A	N/A	N/A	10	10	10	10	10
FSB I^c,d^	5	5	5	5	N/A	N/A	N/A	N/A	N/A	N/A	N/A	N/A
FSB II^c,d^	N/A	N/A	N/A	N/A	5	5	5	5	N/A	N/A	N/A	N/A
FSB III^c,d^	N/A	N/A	N/A	N/A	N/A	N/A	N/A	N/A	5	5	5	5
Cooldown	N/A	5	5	5	5	5	5	5	5	5	5	5
Total exercise per session	15	20	20	30	30	30	30	40	50	50	50	50
Total exercise per week	30	40	40	60	60	90	90	120	150	150	150	150

^a^ROM: range of motion.

^b^N/A: not available.

^c^FSB: functional strength and balance.

^d^Participants will be instructed to repeat the prerecorded videos 2 times per week for the first 5 weeks (week 1-5) and then increase the repetition to 3 times per week for the second 7 weeks (weeks 6-12).

At week 3 and week 6, adherence to the exercise program will be administered using Canvas video analytics. Participants who did not adhere to more than 95% of prescribed video watch minutes will be considered as nonresponders. These individuals will be communicated with by research staff at a prescheduled check-in date and guided to the changes of the program at the second phase intervention period:

#### IBC Group

Participants who are allocated into the IBC group will receive the remaining asynchronous M2M exercise prescriptions and augmented with weekly behavioral coaching. The first session was 50 minutes, and the remaining sessions were approximately 15 minutes. The coaching is designed to improve self-regulatory skills based on prior research and help them stick to the exercise prescription. An example of tailoring the exercise prescribed involves setting a goal of completing the exercise routine 1 time for the upcoming week instead of 3 times. The coach will be trained in motivational interviewing to help the participants modify their exercise habits. Telehealth coaching alone has been shown to increase self-reported physical activity in adults with SCI.

#### Synchronous, Instructor-Led M2M Program

Participants who are allocated into M2M Live will switch to one-on-one, synchronous tele-exercise training with an M2M instructor. M2M Live provides accountability and immediate, tailored feedback along with custom movements and music. Videoconference-delivered exercise has been shown as feasible among adults with SCI. During the first session of M2M Live, the participant will meet 1 time per week with the M2M instructor and perform an exercise session. The session will be video recorded, so participants can go back and complete the remaining sessions of the week.

#### Educational Newsletter

All participants will receive an educational newsletter per week, discussing health behavior change strategies such as goal-setting, planning, and coping with barriers. The purpose is to educate participants on self-regulation strategies and health-promoting behaviors.

### Remote Study Procedures

All study procedures, including screening, consent, data collection, and intervention, are conducted remotely at home. Survey data are collected through REDCap. Participants who complete baseline assessments will receive all equipment via mail and will be randomly allocated to 1 of the 2 M2M interventions. After randomization, each participant will receive an invitation email with a link to the Canvas platform, instructed to create a password, and schedule a check-in date at week 3 or 6 based on the group assignment. Participants will be instructed to perform the exercise program at least 3 times per week. Data collection equipment includes: (1) Chromebook (Lenovo Chromebook or Acer Chromebook 15); (2) Fitbit (Inspire 2, Fitbit); (3) Digital peak flow meter (Peak Flow Meter SMPF-1 and SONMOL); (4) blood pressure monitor (Omron 3 Series Upper Arm, Omron); (5) Two 454-gram wrist weights (Neoprene, thumb hole weights, Biicoon).

### Outcomes

#### Aim 1: Feasibility Metrics

All feasibility outcomes will be collected throughout the 12-week study period. This study will gather metrics of feasibility, including recruitment or enrollment (eg, frequency of contact with potential participants and recruitment sources, with questions such as, Where did you hear about our study? and the percentage of individuals who follow through the enrollment procedure); adherence and retention rates (eg, video watch minutes, attendance of M2M Live or IBC coaching sessions); resources and management issues (eg, preparation and completion time in minutes for functional outcome assessment; time in minutes for survey assessment); timing to identify nonresponders; and AE. The study team will monitor AEs throughout the study period and report them followed by the Behavior Change Consortium of the National Institutes of Health. The four types of AEs are (1) falls, (2) cardiovascular-related episodes, (3) musculoskeletal-related events, and (4) health care use. The severity and causality of each AE will be assessed and will be reported to IRB and relevant regulatory parties when necessary.

#### Aim 2: Acceptability

Acceptability will be assessed qualitatively via thematic analysis of semistructured exit interviews conducted at 3 months from baseline with participants who complete the pilot study.

#### Aim 3: Scientific Outcomes

Table 2 shows the physical and psychosocial outcomes, the schedule of data collection, and instruments used.

**Table 2 table2:** Measures, instruments, and time points.

Variables and instruments			Time point
**Exercise adherence**			
	Tracking exercise video watch minutes (percentage)	12-week intervention period	
**Physical activity**			
	Leisure Time Physical Activity Questionnaire for People with Spinal Cord Injury	Pre or post	
	Postworkout survey	12-week intervention period	
**Lung function**			
	Spirometry	Pre or post	
**Pain intensity**			
	NIH^a^ PROMIS^b^ Pain Intensity Adult Short Form 3a	Pre or post	
**Pain interference**			
	NIH PROMIS Pain Interference Adult Short Form 8a	Pre or post	
**Sleep quality**			
	NIH PROMIS Sleep Disturbance Adult Short Form 8a	Pre or post	
**Fatigue**			
	NIH PROMIS Fatigue Adult Short Form 7a	Pre or post	
**Health-related quality of life**			
	NIH PROMIS 10 Global Health Items	Pre or post	
	NIH PROMIS Ability to Participate in Social Roles and Activities Short Form 8a	Pre or post	
**Exercise enjoyment**			
	Physical Activity Enjoyment Scale	Post	
**Social cognitive theory constructs**			
	Exercise Self-Efficacy Scale	Pre or post	
	Multidimensional Outcomes Expectations for Exercise Scale	Pre or post	
	Exercise Goal-setting and Planning Scale	Pre or post	
	Barriers in Physical Activity Questionnaire–Mobility Impairment	Pre or post	
	Social Provisions Scale	Pre or post	
**Demographics and health history**			
	Questionnaire	Pre	
**Blood pressure**			
	Blood pressure monitor	Pre or post	
**App quality and usability**			
	Systems Usability Scale	Post	

^a^NIH: National Institutes of Health.

^b^Patient-Reported Outcomes Measurement Information Systems.

##### Adherence to the Exercise Program

Video statistics (as a percentage) will be recorded through a secured, commercialized learning management system.

##### Physical Activity

Physical activity will be administered using both objective and self-reported measures. Objective physical activity will be measured using Fitbit throughout the 12-week intervention period, while self-reported physical activity will be measured using the weekly Leisure Time Physical Activity Questionnaire for People With SCI.

##### Postworkout Survey

Weekly survey will be administered within the learning management system to capture the perceived intensity of exercise and any verbatim comments to the program.

##### Physiological Function

All functional teleassessment will be conducted via videoconferencing calls (teleassessments). Data collection toolkits (eg, blood pressure monitors and spirometry) will be mailed to the participants’ location upon the completion of randomization. The data collection will take approximately half an hour and led by an exercise physiology specialist.

##### Psychosocial Health

Psychosocial health outcomes will include pain, sleep, fatigue, perceived exercise enjoyment, quality of life, and SCT constructs. These outcomes will be collected via REDCap. All self-report data will be collected directly through electronic questionnaire packets delivered via REDCap at baseline and post intervention assessments. All question items of the questionnaire packets are made as required to answer to prevent any missing data. Each questionnaire packet is also set to be delivered to participants’ email 3 times, within a span of 3 days if it is not completed. Research staff will be notified via REDCap when the third packet was sent out to participants. A follow-up phone call will be made to ensure participants receive the packet and remind them to complete it within the next 3 days. Packets that are incomplete within the 3 days after the phone call will be closed and recorded as incomplete, missing data.

### Analysis

#### Overview

All data will be exported and analyzed using SPSS (version 22.0; IBM). Data will be initially examined for variations, outliers, errors, and patterns of missing values. Missing data will be inputted using multiple imputation techniques where necessary based on the assumption that the missingness mechanism is at random. All statistical analyses will be conducted in an intent-to-treat manner at the individual level.

#### Aim 1

The primary outcomes of this pilot study will include enrollment rate, retention rate, and completion rate of surveys and physiological measures. Process, resource, and management feasibility will initially be examined via percentage, frequency analysis, and descriptive statistics.

#### Aim 2

A qualitative study of participants’ experiences, perceptions, and suggestions regarding the SMART-HEALTH program will be completed at week 12. This study will refine the study components and implementation processes for a future trial. In brief, participants who complete the SMART-HEALTH program will take part in single, one-on-one semistructured interviews with questions focusing on what worked and did not work. Interviews will be audio-recorded, transcribed, and analyzed using thematic analysis using a qualitative descriptive design [43].

#### Aim 3

The study will estimate recruitment and retention rates, as well as estimate outcomes and variability of efficacy outcomes for a larger clinical trial (aim 3), which will measure rates of physical activity, psychosocial variables (eg, depression), and physiological variables (eg, lung function). Additional fidelity measures will include adherence to exercise intervention (minutes of sessions viewed), number of coaching sessions completed, and intervention safety (number of AEs).

### Power

We will aim to enroll at least 40 people with SCI, considering 25% of the attrition rate based on the preliminary data obtained in the exercise intervention study with the M2M program [44]. The sample size of 30 participants aligns with the statistical recommendations for pilot trials to determine precise estimates, and the expectation that at least 5 participants will move each rerandomization group aligns with the statistical recommendations for the pilot SMART trial to determine precise estimates [45,46].

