## Methods

### Study Design

This pilot study applied a 2-phase SMART design. Thirty adults with SCI will be randomized with equal probability into 1 of 2 asynchronous, M2M exercise programs (using prerecorded videos) at the first phase of the intervention. The exercise minutes of the pre-recorded videos are set to progressively increase from 30 to 150 minutes per week throughout the 12 weeks. The response assessment will be administered at weeks 3 (group 1) and 6 (group 2) based on the predetermined adherence criteria to the intervention (average of 95% video watch minutes, ranging from 29 minutes to 143 minutes). Participants who meet or exceed the criteria will be considered as responders and continue the asynchronous program for the entire intervention period, whereas those who did not meet the criteria (nonresponders) will be rerandomized with equal probability into either synchronous, instructor-led M2M exercise program (ie, switch to M2M Live group) or behavioral coaching with asynchronous M2M exercise program (ie, augment with individual behavioral coaching; IBC). The study flow diagram includes the details of the interventions offered in each arm (Figure 1).

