### Randomization Allocations and Other Trial Considerations

Participants are potentially randomized up to twice throughout the 12-week intervention period. A study statistician generated 3 randomization sequences a priori using a computer-generated random schedule (SAS version 9.4; SAS Institute) with a 1:1 allocation ratio and a permuted block approach. The sequences were stored into a randomization module in the REDCap and external program, which allows project staff to unfold the randomization schedule when needed (after completing baseline assessment and after a 3-week or 6-week check-in call). One sequence was used to perform the first randomization of 30 participants into one of the asynchronous M2M exercise groups (group 1 vs group 2), whereas other 2 sequences were used to perform the second randomization of participants who need a transition from asynchronous M2M exercise to M2M Live or IBC based on the adherence rate to the intervention. Response assessment (ie, adherence rate to the program) will be administered at week 3 and week 6, respectively, for the intervention groups 1 and 2. Participants identified as responders who watched the video more than 95% (accounting for 5% error rate) will continue with the first treatment regime. Participants will be considered nonresponders if they adhere to the exercise program less than 95% using video watch minutes. This is based on observation with a few weight loss studies that suggested sessions 3 and 7 as potential time points for intervening with participants to assess needs and difficulties and make necessary changes to maximize the treatment response [39-42].

The outcome assessor will be blinded to group allocation (single-blinded trial design). Due to the nature of the intervention, it is not plausible to blind participants and study staff who enroll participants and monitor the intervention delivery. However, study investigators and staff who are involved in data analyses and reporting will be blinded to group assignments throughout the study period.

Access to the REDCap database will be given to the study personnel only, including the biostatistician and data entry or management personnel. Data that are analyzed will be exported in a deidentified format. The identities of participants will not be revealed in the presentation or publication of any result from this project.

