### Strength and Limitations

The trial uses an innovative study design to address adherence to exercise interventions among people with SCI. It addresses a growing need among physicians treating patients with mobility disabilities to have easily accessible eHealth home-based exercise videos that can be tailored to the functional level of their patients. This is a pilot trial to assess the feasibility of using a SMART design and is not powered for effectiveness.

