### Conclusions

The trial serves to inform the development of adaptive interventions, including whether, how, or when to alter treatment intensity, type, or delivery. In addition, this can determine the actual efficacy of home-based exercise based on the SCI-specific physical activity programs for improving adherence to the program and physical activity.

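### The Power section makes 30 the number left after 25% attrition from 40, but the design sections randomise 30; the five-per-group, precision and efficacy statements built on that size also need correcting

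*Protocol article*

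**What the plan says.** **Sample size.** The Power section states "We will aim to enroll at least 40 people with SCI, considering 25% of the attrition rate", taking the rate from preliminary data of an exercise intervention study with the M2M programme. It then says "The sample size of 30 participants aligns with the statistical recommendations for pilot trials to determine precise estimates".

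Study Design says "Thirty adults with SCI will be randomized with equal probability into 1 of 2 asynchronous, M2M exercise programs". Randomization Allocations and Other Trial Considerations says "One sequence was used to perform the first randomization of 30 participants into one of the asynchronous M2M exercise groups". The Abstract (Objective) and the Introduction also describe a trial of 30 adults.

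**Re-randomised groups.** The Power section adds an expectation that "at least 5 participants will move each rerandomization group aligns with the statistical recommendations for the pilot SMART trial to determine precise estimates". The randomisation section describes two further sequences for the second randomisation and a 95% watch-minute threshold for response. No expected nonresponse rate is given.

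**Efficacy.** The Conclusions say that "this can determine the actual efficacy of home-based exercise". Strength and Limitations says that the trial "is not powered for effectiveness", and the Introduction leaves the establishment of efficacy to later, larger projects.

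**The concern.** The number 30 has two roles that cannot both hold. In the Power section it is what remains of 40 after attrition; in the design and randomisation sections it is what goes in.

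The figure matters even in a pilot with no powered hypothesis. Enrolment and retention rates are among the primary outcomes (Analysis, Aim 1), and their denominators depend on it. It also fixes how long the first-stage sequence must be, and how likely the article's own expectation of five per re-randomised group is to be met.

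Two further statements claim more than this size and design can give: precision from groups of five, and a determination of efficacy.

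**Working it through.** **1. Reproduce the plan's figure.** Inputs: 30 participants and 25% attrition (Power). N/(1 - d) = 30/(1 - 0.25) = 40. This matches exactly, so in the Power section 30 is the number after attrition.

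**2. Apply the same attrition to the number randomised.** Input: 30 randomised (Study Design; randomisation section). 30 × 0.75 = 22.5, about 22 at week 12. With 40 randomised, 40 × 0.75 = 30.

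**3. Five per re-randomised group, counted at entry.** With 1:1 allocation, 30 randomised gives 15 per first-stage group. The nonresponse rate q is not in the article, so a range is assumed.

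*Four cells* (two timings by two options). Each first-stage group needs at least 10 nonresponders to give 5 + 5. The mean reaches 5 per cell at q = 10/15 = 67%. The chance that all four cells reach 5 is P(Bin(15, q) ≥ 10)², or P(Bin(20, q) ≥ 10)² with 40 randomised. An even second-stage split is assumed, which favours the plan.

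| Assumed q | 30 randomised | 40 randomised |
|---|---|---|
| 50% | 0.02 | 0.35 |
| 60% | 0.16 | 0.76 |
| 67% | 0.38 | 0.93 |
| 70% | 0.52 | 0.97 |
| 80% | 0.88 | 0.999 |
| 90% | 0.996 | 1.00 |

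An 80% chance needs q of about 77% with 30 randomised and about 61% with 40.

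*Two groups* (M2M Live and coaching, each pooled over both timings). Ten nonresponders in total suffice. With 30 randomised, P(Bin(30, q) ≥ 10) = 0.41 at 30%, 0.82 at 40% and 0.98 at 50%.

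**4. Precision.** The 95% half-width for a difference of two means, in SD units, is t(0.975, 2n - 2) × √(2/n).
- n = 5 per cell: 2.306 × √(2/5) = 1.46 SD.
- n = 15 per group: 2.048 × √(2/15) = 0.75 SD.

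An SD estimated from five observations has 95% limits of 0.60 to 2.87 times the estimate (chi-square, 4 df).

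**5. Efficacy, by comparison of the text.** The Conclusions say that the trial can determine efficacy. Strength and Limitations says that it is not powered for effectiveness, and the Introduction assigns efficacy to larger projects. Every arm receives M2M in some form (Study Design; IBC Group; Synchronous, Instructor-Led M2M Program), so no contrast isolates exercise from no exercise.

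**The case against.** **The inflation is correct, and enrolling is not randomising.** Both points stand. A reader might infer an arithmetic error in the Power section; there is none. The article also separates consent (Recruitment and Enrollment) from randomisation after baseline assessment (Remote Study Procedures), so 40 consented and 30 randomised is a possible reading. But it is stated nowhere, it fits poorly with an attrition rate taken from an intervention study, and it leaves no allowance for loss after randomisation. Equally, that 40 must be randomised is an inference from the source of the rate, which cannot be checked here.

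**Thirty may well deliver five per group.** This also stands. A reader might infer that 30 cannot do so, but the article does not support that unconditionally. A strict 95% threshold could produce nonresponse above 80%, at which even the four-cell reading is likely to be met, and the pooled reading needs far less. What remains is that neither the rate nor the meaning of group is stated.

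**Five at week 12 is not what is promised.** A reader might test the expectation against participants with final data. The Power section counts those who move into each group, so the count at entry is the fair test and the only one used here.

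**Cell estimates need not size the larger trial.** The Introduction speaks of average intervention effects and variability, and no cell-by-cell comparison is specified. The article does not say that effects from cells of five will be carried forward.

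**Thirty is ordinary for a feasibility pilot, and the precision wording leans on cited recommendations.** Those sources are not available here, and 30 may be a reasonable pilot size. That does not make estimates from cells of five precise.

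**The efficacy claim is one Discussion sentence.** It drives no analysis, but it contradicts two other statements in the same article.

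**Conclusion.** The conflict over sample size holds: 30 is the post-attrition number in the Power section and the number randomised elsewhere. If the 25% is in-programme loss, the trial as designed expects about 22 at week 12, which is 7 to 8 fewer than 30. If it is loss before randomisation, the article needs to say so and to allow for later loss.

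The five-per-group expectation is unsupported rather than wrong. Under the four-cell reading with 30 randomised, the chance of meeting it runs from 38% at 67% nonresponse to 88% at 80%, assuming an even second-stage split. Under the pooled reading, about 40% nonresponse is enough.

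The precision wording does not fit cells of five, and the efficacy sentence contradicts the article itself. For a feasibility pilot these are points that should be fixed; they do not invalidate the design.

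**What to change.** 1. Use one sample size in the Abstract, Introduction, Study Design, randomisation and Power sections: either 40 randomised with about 30 expected at week 12, or 30 randomised with about 22 expected. Say at which step the 25% loss is expected, and use the number randomised as the denominator for retention.
2. If 40 is confirmed, make sure that the first-stage sequence covers 40.
3. Say whether a re-randomisation group means one of four cells or M2M Live and coaching pooled over timing. State the assumed nonresponse rate and the resulting chance of reaching five.
4. Replace the precision wording with expected interval widths: about 1.46 SD for a difference between two cells of five, and about 0.75 SD for 15 against 15.
5. Delete the statement in the Conclusions that the trial can determine actual efficacy.

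The cost is wording, plus a sequence extension only if 40 is the intended number. No added data collection is needed unless 40 is confirmed and only 30 had been planned.
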